## Abstract

**Background:**

Main risk factor for the development of chronic obstructive pulmonary disease (COPD) is smoking, although only less than 1/3 of smokers develop clinically manifest COPD. COPD’s progressive nature with high disability and mortality makes it plausible to detect it as early as possible thus allowing for an early intervention. The only tool for an early diagnosis that could be used on the global scale is spirometry, even though symptoms and deprivation of health related quality of life (HRQoL) precede relevant spirometric changes. Existing HRQoL questionnaires are too complicated or not developed for an early detection of COPD. The aim of our study was to develop a new simple HRQoL tool that will allow (alone or in combination with other markers) early detection of patients with COPD.

**Methods:**

A multicenter prospective cohort study recruiting 500 subjects at risk for COPD (smokers/ex-smokers ≥20 pack-years, 40–65 years, both sexes, with no prior diagnosis of COPD) will be carried out in two phases: (1) cross-sectional - development and validation of a new questionnaire; and (2) prospective - follow-up of a cohort of patients at risk for COPD. Subjects were recruited by 25 GPs and assessed for COPD by dedicated pulmonologists in 7 hospital centers using a predefined protocol: HRQoL, history, physical, blood sampling, exhaled breath temperature (EBT), lung function, 6-min walk test (6MWT). Patients without COPD and those in GOLD stage 1 at initial assessment will be reassessed for disease progression by the same pulmonologist after 2 and 5 years.

**Discussion:**

This is one of the first cohort studies attempting to establish the incidence of COPD in the pre-symptomatic stage before significant end organ damage. We intend to assess the validity, predictability and discriminative power (‘healthy’ smokers vs. pre-symptomatic phase in newly developed COPD) of newly developed HRQoL tool alone or in combination with other markers; EBT, lung function, 6MWT, genomics, transcriptomics, proteomics). We expect that the results of this study can improve our understanding of the development of COPD, identify some new underlying pathophysiological pathways, and offer to sensitive smokers/ex-smokers new preventive and early intervention measures thus improving the management of COPD.

**Trial registration:**

Clinicaltrial.gov NCT01550679 retrospectively registered February 28, 2012.

## Background

Chronic obstructive pulmonary disease (COPD) is a major cause of morbidity and mortality globally, responsible for approximately 5 million deaths every year, with expected significant rise in mortality untill the year 2020. COPD mortality is low at age 45, but significantly rises after the age of 65 with significant comorbidity already present. COPD has a major economical and public health impact especially with regard to severe disease and exacerbations. Major risk factor for COPD development is tobacco smoke, although only less than 1/3 of smokers develop COPD during their lifetime. Because of its progressive nature COPD ends with early disability and mortality. Stopping or slowing down the progression of the disease is still an unmet need, although therapeutic interventions in COPD patients have shown to have significantly larger impact if they were started earlier in the course of the disease [1–4]. An early diagnosis should allow for an early intervention, thus possibly preventing the progression of COPD, alleviating symptoms and improving general wellbeing, preventing complications and comorbidities and early mortality [5]. The only available method for an early diagnosis that is suitable for screening purposes is spirometry (also used as the ‘gold standard’ for COPD diagnosis). Although screening on a global scale is not recommended by COPD guidelines, recommendations for early diagnosis (case finding) have been heavily advocated [6, 7]. New insights of the genetic background of COPD development have been revealed from cross-sectional large scale genetic studies but these data still need confirmation on a global scale using prospective data [8]. On the other hand, symptoms and loss in health related quality of life (HRQoL) often precede diagnostically relevant loss of lung function (FEV_1_/FVC <0.7 or < lower limit of normal [LLN]) [6]. Consequently we need new simple tools to detect patients in an early (pre)symptomatic stage of COPD before significant end organ damage. Based on these assumptions; the possibility of identifying the population at risk and the possibility of producing significant benefit for the patient if COPD is identified early, we decided to develop and test a new tool (to be used alone and in combination with other markers) in a prospective cohort study in a population at risk (smokers/ex-smokers with significant cumulative exposure to tobacco smoke, with no prior diagnosis of COPD). This new tool should be based on a prerequisite for a screening tool; usable on a global level, cheap, self-applicable, moderate to high sensitivity and high specificity (no false positives) for COPD. As existing HRQoL questionnaires are too complicated (Chronic Respiratory Questionnaire - CRQ, St. George Respiratory Questionnaire - SGRQ), and/or not developed for the purpose of early detection of COPD (Clinical COPD Questionnaire - CCQ, COPD Assessment Test - CAT), we have constructed, developed, and intend to validate a simple self-applicable questionnaire to detect early changes in HRQoL related to future COPD development [9–13].

## Methods

### The aim, design and setting of the study

The aim of this two phase prospective observational cohort study in subjects at risk for COPD was to construct, develop and validate a new tool (newly constructed self-applicable HRQoL questionnaire – MARKO questionnaire) to be used alone or in combination with other markers (exhaled breath temperature [EBT], lung function, inflammatory markers, and omics) in order to identify subjects who will develop COPD, even before significant end organ damage that can be identified using spirometry.

The MARKO study is a prospective, observational, non-interventional cohort study of subjects (both sexes) at risk for the development of COPD (smokers/ex-smokers with a smoking history of ≥20 pack-years), without a previous diagnosis of COPD. The study for all investigational sites was approved by the Children’s Hospital Srebrnjak Ethics Committee and performed in accordance with the Declaration of Helsinki, good clinical practice, and all relevant international and national legislations. According to a national legislation regarding non-interventional studies an approval from a single local ethics committee meets the ethical requirements for such a study. The MARKO study has been carried out with the cooperation of 25 general practitioners (GPs) and 7 tertiary hospital research centers (within Departments of Pulmonology) since 2010 (Table 1).

**Table 1 Tab1:** The list of study sites and researchers involved in MARKO study (MARKO study group)

Study sites	Contact person/researcher	Role
Children’s Hospital Srebrnjak, Zagreb, Croatia	Assoc.[name], MD, MSc, PhD	Principal Investigator
General Hospital Dubrovnik, Dubrovnik, Croatia	[name], MD, MSc	Principal Investigator
University of Liverpool, Liverpool, UK	[name] [name], PhD	Study consultant
University of Zagreb Centre for Croatian Studies, Zagreb, Croatia	Assist.[name] [name], PhD	Psychologist
Institute for Medical Research and Occupational Health, Zagreb, Croatia	Assist.[name], BA, MA, PhD	Psychologist
University Hospital Center Osijek, Osijek, Croatia	[name], PhD	Co-Investigator
	[name], PhD	Subinvestigator
	[name]	Subinvestigator
University Hospital Center Split, Split, Croatia	Assist.[name], MD, PhD	Co-Investigator
Univerity Hospital Center Rijeka, Rijeka, Croatia	Assist.[name] [name], MD, PhD	Co-Investigator
University Hospital Dubrava, Zagreb, Croatia	Assoc.[name], MD, PhD	Co-Investigator
	[name], MD	Subinvestigator
University Hospital Center Zagreb, Zagreb, Croatia	Assoc.[name] [name], MD, PhD	Subinvestigator
Special Hospital for Lung Diseases, Zagreb, Croatia	[name] [name]	Subinvestigator
	[name]	Subinvestigator
General practice offices, Osijek, Croatia	[name], PhD	
	[name]	
	[name]	
	[name]	
	[name]	
	[name]	
	[name]	
	[name]	
	[name]	
General Practice offices, Split, Croatia	[name]	
	[name]	
	[name]	
	[name]	
	[name] [name]	
	[name]	
General Practice offices, Zagreb, Croatia	[name]	
	[name]	
	[name]	
	[name]	
	[name]	
	[name]	
General Practice office, Donji Muć, Croatia	[name]	
General Practice office, Postira, Croatia	[name]	
General practice office, Rijeka, Croatia	Assoc.[name] [name], MD, PhD	
General Practice office, Strmec Samoborski, Croatia	[name]	

*Primary endpoint:* to develop and validate the MARKO questionnaire to be used alone or together with other markers to identify subjects that will develop COPD.

*Secondary endpoints:* (a) to evaluate psychometric characteristics of the MARKO questionnaire; (b) to evaluate if the developed screening questionnaire together with the COPD-6^TM^ measurement discriminates COPD patients with GOLD stage 0 (symptomatic smokers) and GOLD 1 from ‘healthy’ smokers and patients with COPD GOLD 2 or higher based on the evaluation made by the pulmonologist; (c) to determine the rate of progression of COPD in patients with GOLD 0 during the follow-up; (d) to determine the prevalence of concomitant disorders in this population; (e) to identify diagnostic parameters that are most sensitive for early impairment in COPD (best discriminate between COPD GOLD 0 and GOLD 1); (f) to compare the MARKO questionnaire with diagnostic tools used for evaluation of patients (SGRQ, CAT, history, physical, lung function, 6MWT); (g) to assess the prevalence of different stages of COPD (specifically GOLD 0 and GOLD 1) in the population at risk for COPD and in the general population.

MARKO is a two phase study: Phase I - a cross-sectional; Phase II - prospective, observational, non-interventional cohort study. Flow diagram of subjects through the MARKO study is presented in Fig. 1 and all the assessments during the study are summarized in Table 2.

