In Phase I up to 700 subjects will be recruited with the risk of COPD by 25 GP’s offices (representing 25 GPs) in and around 4 major cities. Patients were approached by their GP during any (unrelated to respiratory problems) visit to the GP’s office if they were smokers or ex-smokers of the predefined age group for the study and were prescreened for inclusion/exclusion criteria using a structured interview. Eligible patients were given the Informed consent document with enough time to read it and to discuss any relevant issues regarding the study before consenting. All participants signed written consent for the follow-up study, and separately for bio-banking of blood for omics (DNA, RNA, serum and plasma) before taking part in the study and before any procedure was done. Inclusion criteria for the study were defined as: written consent; smokers/ex-smokers; both sexes; aged 40–65 years at inclusion; smoking history of at least 20 pack-years (calculated as a number of cigarettes smoked per day multiplied by the number of years of smoking divided by 20); and no previous diagnosis of COPD. Exclusion criteria were defined as: any clinically relevant chronic disease (cardiovascular, cerebrovascular, diabetes, hepatitis, nephropathy, chronic dialysis, systemic disorder, cancer) significantly affecting HRQoL; ongoing immunosuppressive therapy; preceding acute respiratory disease 4 weeks before inclusion; hospitalization for any reason during the past 3 months; myocardial infarction (MI), cerebrovascular infarction (CVI) or transient ischemic attack (TIA) during the past 6 months; diagnosis of asthma; and an inability to perform the diagnostic protocol. Exclusion criteria were introduced in order not to exclude patients with comorbidities common in COPD, but to exclude those that represent acute/subacute clinical states/disorders or states of recovery from major clinical disorders representing an absolute or relative contraindication for spirometry or significantly influencing the diagnostic process or an already present diagnosis of respiratory disorder (e.g., asthma). After inclusion patients fill out the self-applicable MARKO questionnaire in the GP’s office and measurement of lung function is done using COPD-6™ (4000 COPD-6™ Respiratory Monitor, Vitalograph Ltd., Buckingham, UK) recording the values of forced expiratory volume in 1 s (FEV_1_), forced expiratory volume in 6 s (FEV_6_ - as a surrogate marker of forced vital capacity [FVC]), FEV_1_/FEV_6_ (as a surrogate marker of FEV_1_/FVC), and lung age. Two to 4 weeks after inclusion eligible patients are referred to one of the 7 tertiary hospital research centers, to a designated team consisting of a pulmonologist, research nurse and lung function laboratory technician where a structured diagnostic workup consisting of the MARKO questionnaire, HRQoL questionnaires (SGRQ and CAT), structured history and physical, exhaled breath temperature (EBT) before (EBTb) and after a smoked cigarette (EBTc), lung function testing with bronchodilator (salbutamol), impulse oscilometry (only in one center), lung diffusion capacity (DL_CO_), body plethysmography (only in one center), blood sampling (hematology; highly sensitive C-reactive protein [hs-CRP]; blood for DNA, RNA, plasma and serum), functional exercise capacity using 6-min walk test (6MWT), ending with the assessment for diagnosis and severity of COPD according to the Global Initiative for Chronic Obstructive Lung Disease (GOLD) and according to the American Thoracic Society/European Respiratory Society (ATS/ERS) recommendation for airway limitation using lower level of normal (LLN) [6, 14].

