Phase I of the MARKO study will be used to test the psychometric characteristics of the MARKO questionnaire; to evaluate discriminative power of the MARKO questionnaire together with COPD-6™ measurements between different developmental stages of COPD; to identify diagnostic parameters that are most sensitive for early impairment in COPD (discriminate between COPD GOLD 0 and 1); to compare the MARKO questionnaire with other measures used to evaluate patients (HRQoL, history, physical, lung function, functional capacity); and to assess the prevalence of different stages of COPD (specifically GOLD 0 and 1) in the population at risk for COPD. Preliminary data from Phase I of initial validation of the MARKO questionnaire showed the potential for the MARKO questionnaire to assess early health status changes in smokers at risk for chronic obstructive pulmonary disease [31]. Although exclusion criteria were introduced to exclude subjects with acute/subacute clinical disorders or states of recovery from major clinical disorders representing an absolute or relative contraindication for spirometry or significantly influencing the diagnostic process, the data analysis showed that more than half (56.3%) of the recruited subjects had one or more (up to 3) comorbidities (28.6% hypertension, 10% dyslipidemia, 5.2% diabetes and 4.9% peptic syndrome, etc.) [31].

Phase II of the MARKO study will be used to test the primary endpoint of the study: to validate the MARKO questionnaire as a tool to be used alone or combined with other markers in identifying subjects at risk (smokers/ex-smokers with relevant exposure to tobacco smoke) who will develop COPD during the follow-up. Based on previously published data that EBT could be a sensitive marker of airways inflammation [21] we introduced it as a possible predictive marker for future COPD. Recently published data from Carpagnano GE et al., and from our group (preliminary data from the MARKO study) showed the sensitivity of EBT to cigarette smoke and the potential to predict future development of COPD in current smokers [32, 33]. All other parameters were measured/gathered at the start of the study for a detailed phenotype/endotype of recruited subjects and as possible predictive markers for future COPD.

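### Secondary endpoint (g) promises COPD prevalence in the general population, which a cohort of undiagnosed heavy smokers cannot estimate at any sample size

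*Protocol article*

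**What the plan says.** All places are in the protocol article.

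- **Methods, The aim, design and setting of the study, secondary endpoint (g):** the prevalence of COPD stages, specifically GOLD 0 and GOLD 1, is to be assessed "in the population at risk for COPD and in the general population".
- **Same section, Phase I paragraph:** 25 GP offices recruit up to 700 subjects. Eligible patients are smokers or ex-smokers aged 40–65, with a "smoking history of at least 20 pack-years" and no earlier COPD diagnosis. They are approached at GP visits made for non-respiratory reasons.
- **Same section, Phase II paragraph:** up to 500 subjects are taken from Phase I. No new source of subjects is opened.
- **Background:** the tool is to be tested "in a population at risk (smokers/ex-smokers with significant cumulative exposure to tobacco smoke, with no prior diagnosis of COPD".
- **Discussion, use of Phase I data:** the prevalence aim reads "to assess the prevalence of different stages of COPD (specifically GOLD 0 and 1) in the population at risk for COPD". The general population is not mentioned.

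**The concern.** A prevalence needs a sample, or a sample plus outside data, that covers the population it refers to. Endpoint (g) names two populations, and the design samples only one of them. If the objective stays as written, the study either leaves a stated secondary endpoint unreported or reports a proportion among heavy smokers under a general-population label. Smoking is the risk factor on which subjects are selected, so the second outcome would be a serious misstatement. The article also gives two versions of the same aim, and a reader cannot tell which one binds.

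**Working it through.** **1. The two statements of the aim**

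| Place | Stages | Target population |
|---|---|---|
| Methods, endpoint (g) | GOLD 0 and GOLD 1 specifically | At-risk and general population |
| Discussion, use of Phase I | GOLD 0 and 1 specifically | At-risk population only |

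Stages and purpose are the same; the target differs. Phase II cannot supply the missing half, because its subjects all come from Phase I.

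**2. What the sample covers**

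Everyone enrolled meets four conditions together: smoker or ex-smoker, age 40–65, at least 20 pack-years, no prior COPD diagnosis. Anyone failing one of them has zero chance of selection. The article describes no second sample, weighting scheme or external rates for these people.

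**3. What the data can say about the general population**

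Let *s* be the share of the general population that is eligible, *p* the prevalence among the eligible, and *q* the prevalence among everyone else. Then

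P(general) = *s* × *p* + (1 − *s*) × *q*.

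The study informs *p* only. With *q* free between 0 and 1, the result lies between *s* × *p* and *s* × *p* + (1 − *s*). The width of that interval is 1 − *s*, which does not depend on the number enrolled.

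For *p*, the Data analyses section expects 75% healthy and symptomatic smokers, 12.5% GOLD 1, 6.25% GOLD 2 and 6.25% GOLD 3 or 4. These sum to 100%, and 12.5 + 6.25 + 6.25 = 25% have airflow limitation. GOLD 0 has no expected share of its own; it sits inside the 75%. The documents do not give *s*, so 5% and 30% are assumptions used for illustration only.

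| *s* (assumed) | GOLD 1, *p* = 12.5% | GOLD 1–4, *p* = 25% |
|---|---|---|
| 5% | 0.05 × 0.125 = 0.6% up to 0.6 + 95 = 95.6% | 0.05 × 0.25 = 1.25% up to 96.25% |
| 30% | 0.30 × 0.125 = 3.75% up to 73.75% | 0.30 × 0.25 = 7.5% up to 77.5% |

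These ranges show only that the quantity is not identified. They do not measure the size of an error.

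**4. The at-risk half of (g)**

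Under the Background definition the sampled group and the target agree on exposure and diagnosis status. The 95% half-width is 1.96 × √(*p*(1 − *p*)/*n*), ignoring clustering by GP:

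- *p* = 25%: 3.8 percentage points at *n* = 500, 3.2 at *n* = 700.
- *p* = 12.5% (GOLD 1): 2.9 points at *n* = 500, 2.45 at *n* = 700.

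This half is estimable with useful precision.

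**The case against.** The strongest defence is that this is a condensed article, that (g) is the last of seven secondary endpoints, and that the Discussion already gives the narrower aim. A full protocol might name an outside source for the general population. It is fair that the point is limited: the primary endpoint, sample size, recruitment and follow-up are untouched. But the article does not merely omit detail. It states an objective that its own recruitment rules cannot meet, and then states the aim differently elsewhere.

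A reader might infer more than this, in three ways that the documents do not support.

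- **That the at-risk half of (g) also fails, because diagnosed cases are left out and the result is biased low.** The Background makes absence of a prior diagnosis part of the at-risk population, so leaving out known cases belongs to the target. Nor is the direction of bias shown. The recruitment rule concerns the reason for the visit and does not bar people with respiratory symptoms, and symptomatic smokers are expected in the sample. GP attenders who accept a hospital work-up could have more disease as easily as less.
- **That endpoint (d) is wrong.** It aims "to determine the prevalence of concomitant disorders in this population", which makes no wider claim. The exclusion of "any clinically relevant chronic disease (cardiovascular, cerebrovascular, diabetes, hepatitis, nephropathy, chronic dialysis, systemic disorder, cancer) significantly affecting HRQoL" does remove some comorbidity. But the Methods say that the criteria were not meant to remove comorbidities common in COPD, and the Discussion reports 56.3% with comorbidities among those recruited, in the same sentence that recalls the exclusions. Read as conditional on those criteria, (d) stands.
- **That general-population prevalence would be overstated by some definite factor.** Any such factor needs the eligible share and the prevalence outside it, and neither is in the documents. A calculation from the 25% would also use GOLD 1–4, whereas (g) names GOLD 0 and GOLD 1.

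**Conclusion.** The point holds for the general-population half of (g) only. That prevalence cannot be estimated from this design at any sample size, and endpoint (g) and the Discussion disagree on the target. The conclusion rests on the eligibility criteria and on the absence of any other described sample, weighting or external source; it needs no numerical assumption. No size for the resulting error can be derived from the documents. It is a wording fault in a secondary endpoint that matters because it governs what the study may claim.

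**What to change.** Delete the reference to the general population from secondary endpoint (g), so that it agrees with the Discussion. State (g) as the proportion with previously undiagnosed COPD by stage (specifically GOLD 0 and GOLD 1) in the eligible at-risk population as the Background defines it. Naming the undiagnosed status in the endpoint is worthwhile because one sentence of the Discussion describes subjects at risk by tobacco exposure alone.

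Endpoint (d) needs no change; its results should be read as conditional on the exclusion criteria.

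The cost is a wording change to one secondary endpoint and the loss of one claim that the study could not have supported. No data, visits or subjects are added.

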**Fig. 1 Fig1:**
[figure not shown]
Flow chart of subjects through the MARKO study

**Table 2 Tab2:** List of subjects’ assessment through different stages of MARKO study

Assessment	Time/place						
	0	2-4	6	12	18	24	60
		w	m	m	m	m	m
	GP	P	GP	GP	GP	P	P
Prescreening	X						
Informed consent	X						
Inclusion/exclusion criteria	X						
MARKO questionnaire	X	X				X	X
CAT		X				X	X
SGRQ		X				X	X
History		X				X	X
Physical		X				X	X
EBT before and after cigarette		X					
Lung function							
COPD-6™	X	X	X	X	X		
Spirometry with bronchodilator test		X				X	X
Impulse oscilometry^a^		X					
Lung diffusion capacity		X					
Body plethysmography^a^		X					
Blood sampling (hematology; highly sensitive C-reactive protein; blood							
stored for DNA, RNA, plasma and serum)^b^		X					
Functional exercise capacity (6-minute walk test)		X					
COPD diagnosis		X				X	X

Legend: w - week, m - month, GP - general practitioner’s office, P - pulmonologist at tertiary care hospital, CAT - COPD Assessment Test, SGRQ - St. George Respiratory Questionnaire, EBT - exhaled breath temperature

^a^Impulse oscilometry and body plethysmography was done only in one center

^b^Blood sampling was done only in subjects that signed additional Informed consent

In Phase I up to 700 subjects will be recruited with the risk of COPD by 25 GP’s offices (representing 25 GPs) in and around 4 major cities. Patients were approached by their GP during any (unrelated to respiratory problems) visit to the GP’s office if they were smokers or ex-smokers of the predefined age group for the study and were prescreened for inclusion/exclusion criteria using a structured interview. Eligible patients were given the Informed consent document with enough time to read it and to discuss any relevant issues regarding the study before consenting. All participants signed written consent for the follow-up study, and separately for bio-banking of blood for omics (DNA, RNA, serum and plasma) before taking part in the study and before any procedure was done. Inclusion criteria for the study were defined as: written consent; smokers/ex-smokers; both sexes; aged 40–65 years at inclusion; smoking history of at least 20 pack-years (calculated as a number of cigarettes smoked per day multiplied by the number of years of smoking divided by 20); and no previous diagnosis of COPD. Exclusion criteria were defined as: any clinically relevant chronic disease (cardiovascular, cerebrovascular, diabetes, hepatitis, nephropathy, chronic dialysis, systemic disorder, cancer) significantly affecting HRQoL; ongoing immunosuppressive therapy; preceding acute respiratory disease 4 weeks before inclusion; hospitalization for any reason during the past 3 months; myocardial infarction (MI), cerebrovascular infarction (CVI) or transient ischemic attack (TIA) during the past 6 months; diagnosis of asthma; and an inability to perform the diagnostic protocol. Exclusion criteria were introduced in order not to exclude patients with comorbidities common in COPD, but to exclude those that represent acute/subacute clinical states/disorders or states of recovery from major clinical disorders representing an absolute or relative contraindication for spirometry or significantly influencing the diagnostic process or an already present diagnosis of respiratory disorder (e.g., asthma). After inclusion patients fill out the self-applicable MARKO questionnaire in the GP’s office and measurement of lung function is done using COPD-6™ (4000 COPD-6™ Respiratory Monitor, Vitalograph Ltd., Buckingham, UK) recording the values of forced expiratory volume in 1 s (FEV_1_), forced expiratory volume in 6 s (FEV_6_ - as a surrogate marker of forced vital capacity [FVC]), FEV_1_/FEV_6_ (as a surrogate marker of FEV_1_/FVC), and lung age. Two to 4 weeks after inclusion eligible patients are referred to one of the 7 tertiary hospital research centers, to a designated team consisting of a pulmonologist, research nurse and lung function laboratory technician where a structured diagnostic workup consisting of the MARKO questionnaire, HRQoL questionnaires (SGRQ and CAT), structured history and physical, exhaled breath temperature (EBT) before (EBTb) and after a smoked cigarette (EBTc), lung function testing with bronchodilator (salbutamol), impulse oscilometry (only in one center), lung diffusion capacity (DL_CO_), body plethysmography (only in one center), blood sampling (hematology; highly sensitive C-reactive protein [hs-CRP]; blood for DNA, RNA, plasma and serum), functional exercise capacity using 6-min walk test (6MWT), ending with the assessment for diagnosis and severity of COPD according to the Global Initiative for Chronic Obstructive Lung Disease (GOLD) and according to the American Thoracic Society/European Respiratory Society (ATS/ERS) recommendation for airway limitation using lower level of normal (LLN) [6, 14].

In Phase II up to 500 subjects will be recruited from Phase I, assessed by designated pulmonologists as ‘healthy’ smokers, symptomatic smokers (GOLD 0) and as COPD GOLD 1. Selected subjects will be followed for at least 5 years; first assessment after 2 years (±2 months) and the second 5 years (±2 months) after the baseline. During the first 2 years of follow-up all subjects will have regular lung function measurement using COPD-6^TM^ at their GP’s office in 6 month intervals. All subjects will be assessed by the same pulmonologist for diagnosis and severity of COPD according to GOLD and ATS/ERS after 2 and 5 years for the progression of disease defined by three outcome measures: (1) newly diagnosed COPD (ND COPD); (2) disease progression (DP; newly diagnosed COPD + progression to higher severity stage); and (3) high rate of loss of lung function (LoLF; >70 mL/year for post bronchodilator FEV_1_). Incidence of newly diagnosed COPD after 2- and 5-years of follow up will be used to identify diagnostic parameters that are most sensitive for early impairment in COPD, to determine the predictability of developed screening MARKO questionnaire alone or with other markers of early impairment in COPD. Blood samples from a subsample of patients who give the consent for omics research will be used to develop omics markers predictive for the future development of COPD and disease progression.

This research will attempt to answer to following questions: (1) can we identify cheap and simple tools that will allow a precise and accurate identification of subjects from a population at risk of developing COPD in the future; (2) is there a combination (pattern) of tools, functional parameters, genetic and biochemical markers that can reliably predict the development of COPD in a population at risk, thus allowing early intervention.

